#### Tertiary outcomes: efficacy and economics

Efficacy outcomes: Number and proportion of teeth with decay progression at tooth surface level between trial armsNumber of teeth with decay arrest at tooth surface levelNumber of teeth with no change in decay at surface levelEconomic Outcomes:The following outcomes will provide preliminary evidence for the cost-effectiveness of the interventionUse of health resources relating to dental care (general dental or medical practitioner visits, domiciliary care visits, out of hours’ emergency dental center visits) for the intervention year versus the year preceding the study collected from resident’s care recordsUse of health resources for delivery of the intervention (dental team hours, resources, medicinal products) from data collection forms completed by dental team.Use of resources in the home (carers time, administrative hours) from data collection forms completed by care teamCompare the above between the trial arms

### Randomisation

Randomisation will be at the care home level. (i.e. site level).

Residents will be screened for eligibility at each site, and demographic data (age, gender, level of supportive care) will be collected. This will then be used to assess distribution of participant characteristics between the arms, and if a minimisation algorithm needs to be used. This will minimise for age (65–84 vs 85 +), gender (male vs female) and level of supportive care (nursing vs residential) where possible.

Randomisation service will be provided by The UKCRN registered Institute of Kings Clinical Trial Unit. Randomisation will be to a 1:1:1 ratio, undertaken within 7 days of the final baseline resident examination.

As the trial is an open label no emergency code break is required.

### Follow up of participants

Participants will be followed up over 12 months (Table 1).

**Table 1 Tab1:** Trial procedures by visit

Visit	Procedures to be performed
Screening	Complete process for written informed consent with resident or legal representative (including mental capacity assessment)
	Gather demographic information
	Complete medical history
	Review concomitant medications
	Brief oral examination
	Eligibility assessment
Baseline examination (within 28 days of screening)	Changes to mental capacity
	Examination using ICDAS root caries scoring system undertaken by blinded assessor
	Review concomitant medications
	Adverse event monitoring
	Undertake in depth interviews with residents to consider acceptability, QoL (OIDP and EQ5D5L and EQ5D3L survey tool) and relative need (IoRN2)
	Compliance check
	IMP administration
	Reissue 1450 ppm fluoride toothpaste to Arm1 and Arm 3 and 2800 ppm to Arm 2
	Placement of fluoride varnish by trained hygienist to Arm 3
	Complete qualitative interviews with organisational teams
	Brushing charts to be issued
	Collect health care use data for year preceding and intervention year
	Collect resource costs data from the care home
	Completion of data collection forms for resource cost data from the care home/ dental team
Randomisation	Randomisation of homes within 7 days of last baseline visit
3 months from baseline (± 3 days)	Assess changes to mental capacity
	Review concomitant medications
	Adverse event monitoring
	Administer QoL (OIDP and EQ5D survey tools) and relative need (IoRN2)
	IMP administration
	Reissue 1450 ppm fluoride toothpaste to Arm1 and Arm 3
	Reissue 2800 ppm fluoride toothpaste to Arm 2
	Placement of fluoride varnish by trained hygienist to Arm 3
	Brushing charts to be issued
6 months from baseline (± 3 days)	Assess changes to mental capacity
	Examination using ICDAS root caries scoring system undertaken by blinded assessor
	Undertake in depth interviews with residents to consider acceptability, QoL (OIDP and EQ5D survey tools) and relative need (IoRN2)
	Compliance check
	Review concomitant medications
	Adverse event monitoring
	IMP administration
	Reissue 1450 ppm fluoride toothpaste to Arm1 and Arm 3
	Reissue 2800 ppm fluoride toothpaste to Arm 2
	Placement of fluoride varnish by trained hygienist to Arm 3
	Brushing charts to be issued
	Collect health care use data for year preceding and intervention year
	Collect resource costs data from the care home
	Completion of data collection forms for resource cost data from the care home/ dental team
9 months from baseline (± 3 days)	Assess changes to mental capacity
	Review concomitant medications
	Adverse event monitoring
	Compliance check
	Administer QoL (OIDP and EQ5D survey tools) and relative need (IoRN2)
	IMP administration:
	Reissue fluoride toothpastes to control and one intervention arm
	Placement of fluoride varnish by trained hygienist to one arm
	Brushing charts to be issued
12 months from baseline (± 3 days) (end of trial)	Assess changes to mental capacity
	Examination using ICDAS root caries scoring system undertaken by blinded assessor
	Compliance check
	Review concomitant medications
	Adverse event monitoring
	Undertake in depth interviews with residents to consider acceptability, QoL (OIDP and EQ5D survey tools) and relative need (IoRN2)
	Complete qualitative interviews with organisational teams
	Collect health care use data for year preceding and intervention year
	Collect resource costs data from the care home
	Completion of data collection forms for resource cost data from the care home/ dental team

### Statistical analysis

#### Sample size

This is a feasibility study where the primary objective is to assess and estimate the magnitude of feasibility parameters. Consequently, no formal sample size is required for the feasibility parameters. However, assuming a change from baseline to 12 months in the active to arrested mean number of lesions of 0.28 for the control group and a pooled standard deviation of 0.65 [19] and further assuming the experimental interventions are likely to yield at least 50% of the effect of that observed in [19] for the intervention group (i.e. about 0.68 lesions per tooth), based on a reduced concentration (2800  ppm) being used in this study (5000 ppm), the sample size required is 60 per group (180 in total) to achieve at least 84% power to detect a difference (in the change from baseline) of at least 0.4 lesions. For a cluster randomized trial this assumes 3 clusters (2 care homes per group), with an average of 30 subjects per care home, an intra cluster correlation coefficient (ICC) of at least 0.01 and a 2-sided type I error of 5%. Withdrawn patients will not be replaced.

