#### Tertiary outcomes: efficacy and economics

Number and proportion of teeth with decay progression/no change/arrest at tooth surface level between trial arms: The number of teeth with decay progression no change/arrest will be modelled in terms of treatment group and covariates (stratification variables), considering clustering. The mean number of teeth will be presented along with 95% confidence intervals for the difference. The number of teeth with decay progression will be expressed as a percentage and subject to a similar model based approach.Statistical Analysis of HRQoL Endpoints: The EQ-5DL will be presented by each of the 5 domains descriptively. In addition, the raw responses will be converted into utilities and the mean difference between treatments presented along with 95% CIs. In addition, the quality adjusted life year (QALY) will be constructed to provide preliminary estimates of QALYs which will also be compared between groups.Statistical Analysis of Economic Endpoints: Health resource use will be summarised by treatment group. The costs associated with health resource use will also be summarised.

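### The 84% power is stated for lesions turning from active to arrested, whereas the arrest outcome that is listed and analysed counts teeth and has no mean or SD on that scale

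*Protocol article*

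**What the plan says.** The Sample size section first says that the feasibility parameters need no formal calculation. It then gives one for efficacy. The control assumption is "a change from baseline to 12 months in the active to arrested mean number of lesions of 0.28 for the control group", taken with "a pooled standard deviation of 0.65" from the cited care-home trial of 5000 ppm toothpaste. The intervention value is given as "i.e. about 0.68 lesions per tooth". The conclusion is 60 residents per group, 180 in all, "to achieve at least 84% power to detect a difference (in the change from baseline) of at least 0.4 lesions", with an ICC of 0.01, about 30 residents per home and a two-sided 5% test.

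The outcome list (Tertiary outcomes: efficacy and economics) counts teeth in three classes: progression, arrest and no change. The analysis section of the same name follows it: "The number of teeth with decay progression no change/arrest will be modelled in terms of treatment group". It allows for covariates and clustering, and reports mean numbers of teeth with a 95% confidence interval for the difference. Progression is also expressed as a percentage.

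Table 1 schedules the caries assessment at baseline, 6 and 12 months: "Examination using ICDAS root caries scoring system undertaken by blinded assessor".

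**The concern.** A power figure informs the reader only if its difference and SD are on the scale of the variable to be compared. Here the sizing is in lesions, and the outcome list and analysis are in teeth. One tooth can carry several lesions, so the mean and SD of a lesion count are not the mean and SD of a tooth count. The unit is also unsettled inside the calculation itself, which uses a number of lesions for control, lesions per tooth for the intervention and lesions for the difference.

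Two things are at stake. This calculation is the only stated basis for 180 residents, and a reader may take the 84% to describe the arrest comparison that will be reported. In addition, feasibility Criterion 3 asks whether the variability seen makes a full-scale trial achievable. If variability is estimated only on tooth counts, the trial cannot check the 0.65 on which it was itself sized.

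**Working it through.** **Inputs, all from the Sample size section:** control change 0.28; intervention change about 0.68; SD 0.65; n = 60 per group in 2 homes of about 30; ICC 0.01; two-sided alpha 0.05.

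**Step 1. Internal unit.** 0.68 - 0.28 = 0.40, which is the stated difference. The subtraction is meaningful only if 0.28, 0.68 and 0.4 share one unit. The per-tooth label on 0.68 is therefore inconsistent with the labels on the other two figures.

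**Step 2. Reproduce the stated power.**
- Design effect = 1 + (30 - 1) × 0.01 = 1.29.
- Effective n per group = 60 / 1.29 = 46.5.
- Standard error of the difference = 0.65 × √(2/46.5) = 0.135.
- 0.40 / 0.135 = 2.97.
- Power = Φ(2.97 - 1.96) = Φ(1.01) = 84.3%.

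This agrees with the stated 84% (normal approximation, no losses). The arithmetic is sound on its own inputs.

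**Step 3. Compare the variables.**
- Sizing: 12-month change in lesions going from active to arrested.
- Outcome list: number of teeth showing arrest, judged at surface level.
- Analysis: number of teeth in each class, modelled by arm, with a confidence interval for the difference in mean number of teeth.

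Arrest appears in all three places. The lesion count appears only in the first.

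**Step 4. What power would the tooth count have?** The article gives neither a mean nor an SD in teeth, so no single figure follows. As an assumption only, keep the 0.4 difference, n = 60 and design effect 1.29, and vary the SD:

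| Assumed SD (teeth) | SE = SD × √(2/46.5) | 0.4/SE | Power |
|---|---|---|---|
| 0.65 | 0.135 | 2.97 | 84% |
| 0.80 | 0.166 | 2.41 | 67% |
| 1.00 | 0.207 | 1.93 | 49% |

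These rows are illustrations, not estimates. The difference in teeth need not be 0.4, and the SD in teeth could also be below 0.65. Power depends on the ratio of difference to SD, and the article does not give that ratio for teeth.

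**The case against.** The strongest reply is that arrest of decay is a listed outcome and its comparison between arms is planned, with clustering allowed for. A reader might infer that the trial was sized on an endpoint that it neither lists nor analyses, so that the power belongs to no planned comparison. The documents do not support that: the construct is the same and only the counting unit differs. The 84.3% would also hold for any outcome with the same ratio of 0.4 to 0.65. The article leaves open whether teeth have that ratio; it does not show that they lack it. Both parts of this reply stand.

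Three other strong readings also fail.
- A reader might multiply 0.68 per tooth by the average of 14 teeth in the Background (about 9.5) and set that against 0.4. That compares an arm mean with a between-arm difference. The 14 also comes from a general survey of people over 85 with natural teeth, whereas the Background says people in care have fewer and the trial admits residents with 5. Because the three figures subtract correctly, the per-tooth label looks more like a stray phrase than a hidden scaling error.
- A reader might see a contradiction between outcomes at surface level and a root examination. A root surface is a tooth surface, so the outcome wording is at most less specific than the examination.
- A reader might conclude that the unit must be lesions per resident. What 0.28 and 0.65 measure is fixed by the cited trial, which is not at hand.

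It is also fair to say that efficacy is tertiary and framed as estimation, that no feasibility criterion depends on the 84%, and that Criterion 3 names no variable. This limits the weight of the point. It does not remove the mismatch, which lies in stated text and does not depend on detail that an analysis plan might supply.

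**Conclusion.** The point holds as a mismatch of unit. The 60 per group and 84% are correctly computed for a lesion measure with difference 0.4 and SD 0.65. The arrest outcome to be reported is a tooth count, for which no mean or SD is given, so the 84% is not shown to apply to it. If the 0.4 carried over, power would run from about 84% to 49% as the assumed SD goes from 0.65 to 1.0 teeth. That range rests wholly on the assumption, and the article neither confirms nor excludes any value in it. Separately, the per-tooth label on 0.68 conflicts with the subtraction that yields 0.4.

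The consequence is modest, since the primary purpose is feasibility. It is still worth correcting, because this calculation is the sole stated basis for 180 residents and the correction is cheap.

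**What to change.** 1. In Sample size, check 0.28, 0.68 and 0.65 against the cited trial and state one unit for all three and for the 0.4 difference.
2. Add the sizing variable to the efficacy outcomes and to their analysis: the change from baseline to 12 months in root lesions going from active to arrested, in the unit settled under item 1, derived from the ICDAS root examinations already scheduled. Keep the tooth-count outcomes beside it.
3. Estimate the SD and ICC of that variable for Criterion 3, so that the planning SD can be checked and carried into the sizing of a full trial.
4. If the lesion measure is not added, say in Sample size that the 84% applies to the lesion measure only and not to the tooth-count outcomes.

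Items 1 to 3 cost one derived variable and wording changes in three sections, with no new examination. Item 4 costs one sentence, but leaves the planning SD unchecked.

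### The stated 84% power is a ceiling rather than a floor, and holds only if between-home variance is taken as known; the ICC bound is reversed and the cluster count is wrong

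*Protocol article*

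**What the plan says.** The Sample size section first says that the feasibility parameters need no formal sample size. It then gives a calculation for the change in lesions from baseline to 12 months:

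- control change: "active to arrested mean number of lesions of 0.28 for the control group"; intervention change: "i.e. about 0.68 lesions per tooth"
- variability: "a pooled standard deviation of 0.65"
- target: "to detect a difference (in the change from baseline) of at least 0.4 lesions"
- result: "the sample size required is 60 per group (180 in total) to achieve at least 84% power"
- clustering: "this assumes 3 clusters (2 care homes per group), with an average of 30 subjects per care home", with "an intra cluster correlation coefficient (ICC) of at least 0.01 and a 2-sided type I error of 5" per cent

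Trial design and setting and Care home recruitment both give six homes. Randomisation says that homes are the unit, allocated 1:1:1. The Quantitative analysis section plans efficacy models that allow for clustering, with 95% confidence intervals for the differences.

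**The concern.** Three things in one paragraph do not fit together.

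1. A power of at least 84% needs an upper limit on the ICC. The text gives a lower limit.
2. The figure appears to come from a design-effect calculation with a normal critical value, or with degrees of freedom counted in residents. Randomisation is by home, and two homes per arm leave very little information on between-home variance.
3. The text says "this assumes 3 clusters (2 care homes per group"), but three groups of two homes make six clusters.

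At stake is how the arm comparison is presented. The protocol names 60 per group as the number required for that power, so a reader would take the comparison to be far better supported than two homes per arm can make it.

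**Working it through.** **Inputs** (all from Sample size unless noted): difference 0.68 − 0.28 = 0.40; SD 0.65; 60 per arm as 2 homes × 30; ICC 0.01; two-sided 5%; six homes randomised 1:1:1 (Trial design and setting; Randomisation).

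**Reproducing the plan's figure**

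- Design effect: DE = 1 + (30 − 1) × 0.01 = 1.29. Effective n per arm = 60 / 1.29 = 46.5.
- SE of the difference = 0.65 × √(2 × 1.29 / 60) = 0.1348.
- Noncentrality = 0.40 / 0.1348 = 2.97.
- Power with a normal critical value = Φ(2.97 − 1.96) = 84.3%.
- With t on 118 resident-level df it is 83.7%.

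The 84% therefore reproduces. Without a design effect the power would be 92.1%. With one cluster of 60 per arm, which is three clusters taken literally, DE = 1 + 59 × 0.01 = 1.59 and power is 76.2%. So the calculation used two homes of 30 per arm at an ICC of about 0.01.

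**Direction of the ICC bound.** Under the plan's own formula, the largest ICC that still gives 84% is 0.0104. Above that, power drops (normal column below). The text supports only 0.01; the larger ICCs are assumptions shown as a range.

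**Cluster count.** 3 groups × 2 homes = 6, and 180 / 30 = 6.

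**Home-level degrees of freedom.** A pairwise comparison uses four homes: 4 − 2 = 2 df, critical value 4.303. Pooling between-home variance over all six homes gives 6 − 3 = 3 df, critical value 3.182. Power is from the noncentral t with the same noncentrality; half-width = critical value × SE.

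| ICC | DE | SE | Power, normal | Power, 3 df | Power, 2 df | Half-width, normal | Half-width, 3 df | Half-width, 2 df |
|---|---|---|---|---|---|---|---|---|
| 0.01 | 1.29 | 0.1348 | 84.3% | 52.5% | 38.2% | 0.26 | 0.43 | 0.58 |
| 0.02 | 1.58 | 0.1492 | 76.5% | 45.3% | 33.1% | 0.29 | 0.47 | 0.64 |
| 0.05 | 2.45 | 0.1858 | 57.7% | 32.4% | 24.2% | 0.36 | 0.59 | 0.80 |
| 0.10 | 3.90 | 0.2344 | 40.0% | 22.6% | 17.6% | 0.46 | 0.75 | 1.01 |

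Simulating home means at ICC 0.01 gave 38.1% for the 2-df test, in agreement. Even at an ICC of zero, tests on 2 and 3 df give only 45.4% and 62.2%. The shortfall therefore comes mainly from the number of homes, not from the ICC value.

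**The case against.** The strongest reply is that this is a feasibility trial. The section says that feasibility needs no formal sample size, efficacy is tertiary, the tertiary objective is to estimate effects, and the planned output is differences with confidence intervals. No stopping rule or progression criterion uses the 84%. This stands, and it limits the severity.

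Second, the 84% is not a slip of arithmetic, since it follows from the stated inputs by the usual design-effect formula. That is so. What is wrong is the claim attached to it. The article names no reference distribution, so the neglect of home-level df is an inference: 2 or 3 df do not give 84%, while normal or resident-level df do.

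Third, the exact replacement depends on the test. A balanced random-intercept analysis that truncates the variance at zero and moves between 3 and 177 df has simulated power of about 56% at ICC 0.01, with type I error of about 4%. So 38% and 52% belong to particular tests and do not bracket every clustered analysis. None of these comes near 84%. The choice of df may properly be left to the analysis plan, and its absence here is not a fault.

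Fourth, the cluster count may be a slip for three groups, and the ICC wording may mean an assumed value of 0.01. Both are plausible, and neither changes the computed figure. The sentence is still wrong as printed.

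**Conclusion.** Wrong as written, of moderate severity. The 84% holds only at an ICC of about 0.01 or less, and only with between-home variance treated as known. At ICC 0.01, tests on home-level df give about 38% (2 df) or about 52% (3 df). The 95% interval half-width is then 0.58 or 0.43, each wider than the 0.4 target, against 0.26 with a normal critical value. These figures assume equal homes of 30, SD 0.65 and no attrition.

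Two stronger readings are not supported. A reader might infer that criterion 3 will be judged against the 84%. That criterion concerns measurement variability and whether a full-scale sample size is affordable, and it does not mention this figure. A reader might also infer that the trial is too small for its purpose, or that a null result will be taken as evidence against fluoride. The primary objective is feasibility, and the Discussion treats fluoride efficacy as already established.

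**What to change.** Rewrite the clustering sentence to state six clusters, two per arm, and an ICC no greater than 0.01. Then do one of the following:

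- drop the power claim; or
- replace it with the power under the planned cluster-level test at ICC 0.01 (about 38% on 2 df for a pairwise comparison, about 52% on 3 df pooled over six homes). Give the half-width that matches the same df (0.58 or 0.43), and a range over ICCs of 0.01 to 0.10 labelled as assumptions.

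In either case, present the efficacy comparison as estimation only. The choice of test can stay in the analysis plan, provided that any figure quoted in the protocol belongs to that test.

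The cost is one paragraph of text and a less favourable stated figure. No further homes or residents are needed.

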### Qualitative

The process of qualitative data analysis will be iterative process, with transcripts being re-read and reviewed throughout for familiarisation and emergence of new themes to inform and evolve the framework.

The data were summarised and catergorised by themes across the transcripts, whilst being mindful to summarise in way that the context and essence of the participants view is not lost by keeping useful expressions and phrases as much as possible and limiting interpretation.

Finally, a description and explanation of these themes will be developed, by cross examining and interrogating the data, to build emerging theories beyond just the facts. We will focus on the explicit accounts provided by the participants as well the social care perspectives on policy and planning.

### Quantitative

#### Primary outcomes: feasibility

Number of participants recruited, retained, consented and lost (drop out) through the trial period in each trial arm. This outcome will be summarized by treatment group using descriptive statisticsCompliance to trial and data collection process by number of examinations completed, mean length of examination, level of supportive need through the trial period in each trial arm. Compliance through a daily diary of the amount of intervention taken will be recorded in a daily diary and summarized over time. The mean compliance will be presented for each treatment group. Where appropriate a model based analysis with average subject compliance as an outcome will be modelled against treatment and stratification variables and considering clustering. A similar approach for the length of examination will also be undertaken. The level of support will be analysed using appropriate categorical methods.Fidelity to the trial processes: The number of time teeth brushed with fluoride toothpaste will be presented by treatment group and compared between groups using model based methods. The number of applications of fluoride varnish per participant will also be presented descriptively. Where appropriate, additional model based analyses maybe conducted to determine whether differences are explained by any of the stratification variables

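### The between-arm comparisons of brushing, EQ-5D utilities and QALYs are stated without the allowance for care home that the plan gives to compliance, examination length and decay

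*Protocol article*

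**What the plan says.** Under Randomisation, the protocol article states: "Randomisation will be at the care home level". The Sample size section says that "this assumes 3 clusters (2 care homes per group), with an average of 30 subjects per care home", with "an intra cluster correlation coefficient (ICC) of at least 0.01 and a 2-sided type I error of 5" per cent. I read this as two homes in each of three arms, six homes in all, which agrees with the six homes given under Trial design and setting.

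The Quantitative section then treats its outcomes unevenly:

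- **Clustering named:** the compliance model; examination length, which is to be handled in a similar way; and the decay outcomes.
- **Clustering not named, comparison between arms stated:** the number of brushings, which "will be presented by treatment group and compared between groups using model based methods"; the EQ-5D, where "the raw responses will be converted into utilities and the mean difference between treatments presented along with 95% CIs"; and QALYs, which are also to be compared between groups.
- **Clustering not named, no comparison specified:** "The level of support will be analysed using appropriate categorical methods".

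Brushing and supportive need are listed among the primary feasibility outcomes.

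**The concern.** When homes are randomised, the uncertainty of a difference between arms has to include variation between homes. The plan recognises this in its sample size and in some of its analyses. Because it names clustering for some outcomes and not for others in the same section, an analyst could reasonably take the difference as intended. A plain mean difference with a 95% confidence interval, or a standard categorical method, treats residents as independent.

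The omission matters most for brushing. Care staff are expected to deliver and record oral care, so residents of one home may have similar brushing counts because they share the same staff. With two homes per arm, a difference between staff teams could then be presented, with too much precision, as a difference between fluoride programmes.

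**Working it through.** **Inputs from the document.** Six homes, two per arm; 30 residents per home; 60 per arm; ICC 0.01 (worded as a minimum); SD 0.65; difference 0.4 lesions; two-sided 5%; stated power at least 84%; attrition criterion below 35%. ICC values above 0.01 are my assumptions.

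**1. Does the plan's own power figure allow for clustering?**

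- Design effect = 1 + (30 − 1) × 0.01 = 1.29.
- Effective size = 60 / 1.29 = 46.5 per arm.
- Power for 0.4 with SD 0.65 at two-sided 5% = 84.3%, which matches the stated 84%.
- Without the design effect, power would be 92.1%.

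So the plan's figure does include a clustering allowance.

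**2. What if a comparison is run on residents without it?**

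The true standard error is √(design effect) times the naive one. The false-positive rate of the naive test is 2 × [1 − Φ(1.96 / √(design effect))].

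| ICC | Design effect | SE ratio, 30 per home | Naive 5% test rejects |
|---|---|---|---|
| 0.01 (plan) | 1.29 | 1.14 | 8.4% |
| 0.02 (assumed) | 1.58 | 1.26 | 11.9% |
| 0.05 (assumed) | 2.45 | 1.57 | 21.1% |
| 0.10 (assumed) | 3.90 | 1.97 | 32.1% |

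At ICC 0.01 the naive interval has 1 / 1.136 = 0.88 of the width that the design effect calls for, and its coverage is 91.6%. With 35% attrition, leaving 30 × 0.65 = 19.5 residents per home, the rejection rates are 7.2% at ICC 0.01, 15.8% at 0.05 and 24.6% at 0.10.

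**3. What does the small number of homes add?**

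The residual degrees of freedom come from homes:

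- 6 homes − 3 arms = 3, if variance is pooled over the three arms with no home-level covariate. The multiplier is 3.18.
- 4 homes − 2 arms = 2 for a two-arm comparison alone, or 6 − 3 − 1 = 2 with one home-level covariate. The multiplier is 4.30.

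At ICC 0.01 the interval is then 1.136 × 3.18 / 1.96 = 1.84 times the naive width on 3 df, or 1.136 × 4.30 / 1.96 = 2.49 times on 2 df.

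**4. Would any cluster adjustment be enough?**

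Take an uncorrected cluster-robust (sandwich) z test of two arms with two equal-sized homes each. The sandwich variance averages half the true variance, so the z statistic equals √2 times a t variable on 2 df. It rejects when |t| exceeds 1.96 / √2 = 1.386. For 2 df, P(|t| > c) = 1 − c / √(2 + c²). This gives 1 − 1.386 / √3.921 = 0.30. A simulation of 40,000 runs gave the same 30%, while a t test on home means with 3 df held 5%. The ICC does not enter, because the test uses only home means.

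**The case against.** The strongest reply is that silence is not a decision. The article declares a cluster randomised design, builds clustering into its power, and refers to model-based methods for brushing shortly after describing a model-based compliance analysis that allows for clustering. It names no unclustered method, and an article may leave model detail to an analysis plan that is not shown. This stands in part: a reader might infer that the plan has chosen to drop clustering for these outcomes, and the text does not support that. What remains is that clustering is stated selectively within one section, which is more than general brevity.

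Other stronger readings also fail:

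- **That all these outcomes will have confidence intervals and tests that are far too narrow.** Among the outcomes where clustering is not named, 95% intervals are stated only for utilities, and no p-values are planned. At the plan's ICC the design effect alone costs about 12% of the width. The plan's ICC is a minimum and was set for lesions, so brushing could well have a higher one, but the document gives no larger figure.
- **That level of support will be tested between arms as if residents were independent.** No between-arm test is named. The listed outcome is change in supportive need, and nursing and residential care are to be balanced across arms.
- **That an invalid cluster method is planned.** The article specifies no sandwich test and does not exclude a small-sample correction.
- **That the multiplier must be 3.18.** This holds only with variance pooled over three arms and no home-level covariate.

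It is also true that the numerical feasibility criteria (screening, recruitment and attrition) do not depend on these comparisons. That limits the consequence but does not make a resident-level interval correct.

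**Conclusion.** The point holds as an inconsistency that should be corrected, conditional on how the comparisons are carried out. Brushing, utilities and QALYs are to be compared between arms of a cluster randomised trial without the allowance given to neighbouring outcomes; level of support is simply undefined.

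If residents were analysed as independent, the understatement would be modest at the plan's ICC and substantial at an assumed 0.05. These figures assume equal homes of 30 and a normal approximation. The small number of homes is a separate problem that does not depend on the ICC: the 30% false-positive rate applies to an uncorrected cluster-robust z test with two equal-sized homes per arm. It would affect compliance, examination length and decay just as much, so naming clustering is not sufficient without a method suited to six homes.

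**What to change.** State one rule in the Quantitative section that covers every between-arm interval, including those for compliance, examination length and decay: the analysis accounts for care home by one of two methods.

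- Home-level summaries with a t distribution on the cluster degrees of freedom: 3 if variance is pooled over three arms with no home-level covariate, 2 for a two-arm comparison or with one home-level covariate.
- A mixed model with a small-sample correction such as Kenward-Roger.

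Say whether level of support is to be compared between arms at all; if it is, the same rule applies. Tabulate brushing, level of support, utilities and QALYs by home, so that differences between homes within an arm can be seen.

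This changes analysis wording only, with no additional data or residents. The cost is wider intervals, which is what two homes per arm can support.
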